| Statistical Analysis         | 
The HBMC intervention group, control group, and each participating institution will be set as analysis groups for the statistical analysis of the outcome variables.
 
The analysis groups of the participants are based on the group assignment according to the initial intention-to-treat (ITT) that relies solely on the intervention of the original assignment to estimate the effectiveness in the intervention group conservatively. In the case of withdrawal of consent or dropout during follow-up, data collected till the time of withdrawal or dropout will be used. A comparative analysis of the dropout rate between the two groups will be performed and reported.
 
 
- Descriptive analysis of underlying characteristics
 
 
Continuous variables: mean (standard deviation) and median (IQR)
 
Dichotomous variables: frequency (%)
 
 
- Analysis of between-group differences
 
 
An analysis will be performed using a regression model while considering that participants, the observation units, were clustered into six participating institutions to evaluate the effects of the HBMC intervention and correcting for the differences in the baseline characteristics between the groups.
 
Dichotomous variable (primary endpoint): A generalized estimation equation (GEE) will be used to analyze the clusters of patients in participating institutions, and the effects of the HBMC intervention will be evaluated using a logistic regression model based on the logit link function.
 
Continuous variables: The effects of the HBMC intervention will be evaluated using a mixed model to consider the patient clusters in the participating institutions.
 
Count data: A GEE will be used to consider the patient clusters in the participating institutions, and the effects of the HBMC intervention will be evaluated using a regression model that appropriately uses Poisson and negative binomial as random components according to the distribution of variables using the logit link function as the link function.
 |

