## **6. Sample size calculation**

The number of samples for the home-based program required in this study is based on a dichotomous variable, which is the primary endpoint, to secure enough patients for a stable and sufficient power. The primary endpoint of this study is the unplanned hospitalization within six months following enrollment. This study aims to determine the differences in the effects by comparing the odds ratio based on the proportion of unplanned hospitalizations in the intervention and control groups. Although no previous intervention study with a similar design has been conducted outside of Korea, the difference in pre- and post-intervention changes between the intervention and control groups should be approximately 20% (20% less in the intervention group) based on the literature review. The number of institutions in both groups is three. The parameters will be estimated using a generalized estimation equation (GEE) to compensate for the cluster effects of the study participants. The comparisons between the two groups will be analyzed using a logistic regression model, which is used to compare the effects of dichotomous outcome variables while considering other confounding variables. Therefore, a power of 80%, a significance level of 0.05 to control for type 1 error, and a 20% difference in the number of unplanned hospitalizations by intervention was used to calculate the sample size. For a ratio of 1:1 for participants in each group, the minimal sample size should be 396 patients

in total, including 198 patients for three clusters in the intervention groups and 198 patients for three clusters in the control group (assuming within-cluster coefficient=0.015).

Within-cluster coefficient (Intraclass correlation coefficient, ICC) was estimated using the analysis of variance (ANOVA) estimation method according to similar previous studies. The calculation formula is as follows (Sheng et al., 2012; Chen et al., 2015)

In the formula, 
$$n_A = \frac{1}{k-1}(N - \sum n_i^2/N) \quad MSB = \frac{1}{k-1}(\sum Z_i^2/n_i - (\sum Z_i)^2/N)$$

$$MSW = \frac{1}{N-k}(\sum Z_i - \sum Z_i^2/n_i)$$
  $k$  is the number of cluster and  $N$  is the total number of study participants.  $n_i$  and  $Z_i$  are the number of participants in group  $i$  and number of patients with endpoints in group  $i$ , respectively. Incidence rates by group were extracted from a study by Chen et al. (2015) and applied in the present study.

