### ***4) Statistical analysis***

Definition of home-based medical service intervention group and study dropouts: Patients who provided informed consent to the selected home-based medical service intervention institutions and control group institutions are defined as the intervention group and control group, respectively. Based on the principle of group classification by intention-to-treat (ITT) that only considers the initial classification of intervention, omission of home-based medical service is still defined as the intervention group, which causes a bias that reduces the effects in the treatment group. Despite the study's design to conservatively estimate the effects in the treatment group, if significant differences are observed in the results among patients who withdraw consent or dropout during follow-up, data up to the point of withdrawal of consent or dropout will be used. Dropout rates will be analyzed and reported for each group.

The mean proportion of unplanned hospitalization will be compared between the intervention and control groups for the primary outcome. The mean of continuous variables and a fraction of dichotomous variables for each item in domains one to five will be compared between the two groups for the secondary outcome. A generalized estimation equation will be used to evaluate intra-group correlations to compensate for clusters of patients in the participating institutions. Survival after enrollment will be compared using the Kaplan-Meier curve and Cox proportional hazard model.

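### The stated power (83.0% at 396 patients, 78.8% at 342) ignores that six hospitals leave 4 degrees of freedom; a test that holds the 0.05 level has about 58% and 55% on the rates behind the table

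*Protocol*

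**What the plan says.** The Overview (Statistical Analysis) sets a logistic model for the binary primary endpoint: "A generalized estimation equation (GEE) will be used to analyze the clusters of patients in participating institutions". Section 14.B.4 repeats the approach: "A generalized estimation equation will be used to evaluate intra-group correlations to compensate for clusters of patients in the participating institutions". Neither place names a variance estimator, a small-sample correction, a reference distribution or degrees of freedom.

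Section 6 gives the design inputs. On clusters: "The number of institutions in both groups is three". On error control: "a significance level of 0.05 to control for type 1 error". On the effect: "a 20% difference in the number of unplanned hospitalizations by intervention was used to calculate the sample size". On size: "198 patients for three clusters in the intervention groups and 198 patients for three clusters in the control group", with the ICC given as "assuming within-cluster coefficient=0.015". The power target is 80%.

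The power table in Section 6 shows 0.83007 for six clusters of 66 at a labelled ICC of 0.015. With 57 per hospital (342 in all), Section 6 and the Overview both give an expected minimum power of 78.8%. Section 6 concludes that power is sufficient with 396 participants. The arm-specific event rates behind the table are not stated. The only event counts shown are 40 of 198 and 20 of 198, used to estimate the ICC.

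**The concern.** All patients at a hospital are in the same arm, so the treatment effect is judged against variation between hospitals. Three hospitals per arm estimate that variation with 2 + 2 = 4 degrees of freedom. The two-sided 5% critical value of t on 4 df is 2.776, against 1.960 for the normal distribution. A calculation that uses 1.960 treats the between-hospital variance as known and overstates what six hospitals can show.

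The choice of test then matters in one of two ways. A test that allows for six clusters holds the 0.05 level, but its power is well below the printed figure. A test that uses the normal reference of the power table with an uncorrected standard error gives intervals that are too narrow and rejects a true null too often. The trial is meant to support wider use of home-based care, so either a false positive or an undeclared high chance of missing the planned effect would matter.

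**Working it through.** **Inputs.** From Section 6: six hospitals, 66 per hospital (396) or 57 (342), 1:1 allocation, effect 0.2, ICC 0.015, alpha 0.05. Assumed: two-sided test, equal cluster sizes, no covariates. Inferred: 50% versus 30%, because that pair (or its mirror, 70% versus 50%) reproduces the table.

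**Step 1. Reproduce the stated power.**

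- Log odds ratio: ln[(0.5 × 0.7)/(0.3 × 0.5)] = 0.847.
- Variance sum: 1/(0.5 × 0.5) + 1/(0.3 × 0.7) = 8.762.
- Design effect: DE = 1 + (m − 1) × ICC. Effective size per arm: n = 3m/DE.
- z = 0.847/√(8.762/n). Power = Φ(z − 1.960).

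| Hospitals × size | ICC used | DE | n per arm | z | Power, normal | Protocol |
|---|---|---|---|---|---|---|
| 6 × 66 | 0.010 | 1.650 | 120.0 | 3.136 | 0.88014 | 0.88014 |
| 6 × 66 | 0.014 | 1.910 | 103.7 | 2.914 | 0.83007 | 0.83007 (labelled 0.015) |
| 6 × 66 | 0.015 | 1.975 | 100.3 | 2.866 | 0.81756 | – |
| 6 × 66 | 0.020 | 2.300 | 86.1 | 2.656 | 0.75675 | 0.75675 |
| 6 × 57 | 0.015 | 1.840 | 92.9 | 2.760 | 0.788 | 78.8% |

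The rows for 4, 8 and 10 clusters match in the same way. Every row labelled ICC 0.01 or 0.02 agrees to the printed digits, and the rows labelled 0.015 agree at 0.014. The table is therefore normal theory, with no allowance for the number of clusters.

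**Step 2. Same inputs, 4 degrees of freedom.** Power = P(T > 2.776), where T is noncentral t on 4 df with noncentrality equal to z above.

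| Rates | 6 × 66, ICC 0.015 |
|---|---|
| 50% vs 30% | 58.2% |
| 60% vs 40% | 57% |
| 40% vs 20% | 63% |
| 30% vs 10% | 72% |
| 25% vs 5% | 77% |
| 20% vs 10% (rates in the ICC table) | 32% |

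For 50% versus 30% at 6 × 66, power is 65.6% at ICC 0.01, 59.6% at 0.014 and 52.2% at 0.02. At 6 × 57 and ICC 0.015 it is 55.2%. Simulation with beta-binomial clusters, a Kauermann-Carroll-type standard error and t on 4 df gave 58% at 6 × 66 and 55% at 6 × 57.

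**Step 3. Type I error by choice of test.** With three equal clusters per arm, the uncorrected sandwich variance is 2/3 of the unbiased between-hospital variance, because it divides by 3 where 2 is needed. With a normal reference it rejects when |t4| > 1.960 × √(2/3) = 1.600, which has probability 18.5%. Simulation under no effect, at nominal 5%:

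| Test | Rejection rate |
|---|---|
| Uncorrected sandwich, normal reference | 18% (fitted GEE models: 17.7% to 18.8%) |
| Model-based standard error, normal reference | 17% to 19% |
| Kauermann-Carroll, normal reference | 12% |
| Uncorrected sandwich, t on 4 df | 8.4% |
| Mancl-DeRouen, normal reference | 7% |
| Kauermann-Carroll, t on 4 df | 4.8% |
| t-test on six hospital summaries | 5.0% |

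**The case against.** The strongest objection concerns the error rate. A reader might infer that this trial's real type I error is 18%. The documents do not support that. The Overview and Sections 6 and 14.B.4 name GEE, a logit link and clustering on hospital, and stop there. A GEE with a corrected standard error and t on 4 df is consistent with that wording, and such detail is commonly left to a statistical analysis plan, which may exist. The 18% belongs to one unstated choice, and Step 3 shows that other choices give about 5% to 12%. This objection stands: the error rate can only be stated conditionally, and leaving out the correction is not itself the fault.

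Second, the 58% rests on rates that the protocol does not state, and the rows labelled ICC 0.015 match only at 0.014. This also stands, so a range is given. It does not rescue the stated figures: at ICC 0.015 no pair examined reaches 80%. The most favourable pair, 25% versus 5%, would reach 83% at ICC 0.01, but that pair does not reproduce the table and 0.01 is not the planning ICC.

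Third, the figures to compare against are the printed 83.0% and 78.8%; 80% is only the target.

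The objection does not reach the power claim. That claim is printed in the protocol, can be checked there, and is wrong for any test that holds its level with six hospitals.

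**Conclusion.** The point holds as one about stated power, with a conditional consequence for the error rate. On the inferred rates of 50% versus 30% and ICC 0.015, a level-0.05 test has about 58% power at 396 patients, where the table prints 83.0%, and about 55% at 342, where the protocol states 78.8%. Across other 20-point rate pairs the figure at 396 is about 57% to 77%. On the rates in the protocol's own ICC table it is about 32%.

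Whatever a separate analysis plan says, the stated power and the stated alpha cannot both hold. A valid small-sample test loses the power, and an uncorrected sandwich test with a normal reference has a type I error of about 18%. These results assume two-sided testing, equal hospital sizes and no covariate adjustment.

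**What to change.** - **Power (Overview, Number of Study Participants; Section 6).** Replace the normal-theory figures with figures on t with 4 df, and show the assumed arm rates and ICC. With 50% versus 30% and ICC 0.015 these are about 58% at 396 and 55% at 342. Remove the statement that power is sufficient.
- **Analysis (Overview, Statistical Analysis; Section 14.B.4).** Add one sentence: GEE tests and confidence intervals use a small-sample corrected standard error with a t reference on 4 df. Kauermann-Carroll is one choice; a t-test on the six hospital summaries is an equivalent route.

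The cost is a restated calculation, a sentence of text and a few lines of code. Making the analysis valid and the statement accurate needs no extra patients. The downside is wider intervals and a lower stated power, which reopens the question of how many hospitals are enough. For information, on the same basis (50% versus 30%, ICC 0.015, 66 per hospital, hospitals minus 2 df), eight hospitals give 78.7% and ten give 89.8%.

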#### *2) Secondary Efficacy Endpoint*

- Domain 1: The secondary endpoints related to patients' use of medical services and critical care are described below.
  - Number of unscheduled hospitalizations within 6 months of study enrollment (continuous or count variable)
  - Length of hospitalization (total length of hospitalization; continuous variable)
  - History of hospitalization (dichotomous variable)
  - Number of ER visits (continuous variable)
  - Length of ICU hospitalization (total length of hospitalization; continuous variable)
- Domain 2: The secondary endpoints related to patients' quality of life and their satisfaction with the service are described below.
  - Patient's quality of life (EQ-5D; continuous variable)
  - Patient's degree of symptom control (ESAS; continuous variable)
  - Patient's emotional status (PHQ-9; continuous variable)

- Patient's satisfaction with the service (continuous variable)
  
- Domain 3: The secondary endpoints related to the patient's death and preparation of advanced directives are described below.
  - Survival after enrollment (days; continuous variable)
  - Length of ICU hospitalization within 1 month of the patient's death (total length of hospitalization; continuous variable)
  - History of anti-cancer treatment within 1 month of the patient's death (dichotomous variable)
  - Duration of ventilator support within 1 month of the patient's death (total number of days; continuous variable)
  - Preparation of advance directives or physician orders for life-sustaining treatment (dichotomous variable)
  
- Domain 4: The secondary endpoints related to guardians' quality of life and their satisfaction with the service are described below.
  - Guardian's quality of life (EQ-5D; continuous variable)
  - Guardian's emotional status (PHQ-9; continuous variable)
  - Guardian's burden of care (CRA\_K; continuous variable)
  - Guardian's care competency (continuous variable)
  - Guardian's satisfaction with the service (continuous variable)
  
- Domain 5: The secondary endpoints related to medical expenses are described below.
  - Direct medical expenses (continuous variable; KRW)
  - Indirect medical expenses (continuous variable; KRW)

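### Two cluster models are open for most continuous secondary endpoints (mixed model in the Overview, GEE in section 14), and two count endpoints are typed so that either fits

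*Protocol*

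**What the plan says.** Three places in the protocol bear on how secondary endpoints are tested.

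- **Overview, Statistical Analysis** assigns a model by variable type. Dichotomous outcomes get a logistic GEE. For the next type: "Continuous variables: The effects of the HBMC intervention will be evaluated using a mixed model". For the third: "Count data: A GEE will be used to consider the patient clusters in the participating institutions", with a regression that "appropriately uses Poisson and negative binomial as random components according to the distribution of variables using the logit link function as the link function".
- **Section 14.B.4** sets out the secondary comparison: "The mean of continuous variables and a fraction of dichotomous variables for each item in domains one to five will be compared". The next sentence reads: "A generalized estimation equation will be used to evaluate intra-group correlations to compensate for clusters of patients in the participating institutions". No mixed model appears in section 14. Survival has its own Kaplan-Meier and Cox analysis.
- **Section 12.A.2, Domain 1** lists "Number of ER visits (continuous variable") and "Number of unscheduled hospitalizations within 6 months of study enrollment (continuous or count variable").

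Section 12.C.2 calls the intervention effective on a secondary endpoint when the group means differ at the 0.05 level. Nothing says whether the Overview or section 14 takes precedence.

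**The concern.** Read as written, a continuous endpoint such as EQ-5D, ESAS, PHQ-9, caregiver burden, length of stay or cost goes to a mixed model under the Overview and to GEE under section 14. ER visits go to the mixed model by their printed type, or to the Poisson or negative binomial GEE by their nature. The number of unscheduled hospitalizations is left open between the two.

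With only three hospitals per arm, these methods can give materially different p-values on the same data. Either analysis could later be presented as the prespecified one, and section 12.C.2 turns the chosen p-value into a statement of effectiveness.

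**Working it through.** **Inputs from the protocol (section 6).** Three hospitals per arm, 66 patients per hospital, ICC 0.015, alpha 0.05. The ICC follows from the tabulated mean squares: (0.20202 − 0.127946) / (0.20202 + 38.6 × 0.127946) = 0.0144. The protocol gives no error rate for the secondary analyses, so there is no stated figure to reproduce.

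**Assumptions.** Two-sided test, normal outcome, equal hospital sizes, no baseline covariates, identity link. The protocol names neither a variance correction nor a reference distribution, so several are shown.

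**GEE.** Let d be the difference in arm means. Let SS be the sum, over both arms, of squared deviations of the hospital means from their arm mean (3 + 3 − 2 = 4 degrees of freedom).

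- Unbiased variance of d: (SS/4) × (1/3 + 1/3) = SS/6, so d/√(SS/6) follows t on 4 df when there is no effect.
- Uncorrected sandwich variance: SS/9. The robust z is then √1.5 times that t, and |z| > 1.96 means |t| > 1.96/√1.5 = 1.600. Null rejection rate: **18.5%**, whatever the ICC.
- Kauermann-Carroll correction (squared residuals divided by 1 − 1/3): SS/9 × 1.5 = SS/6. On 4 df the rate is **5.0%**.
- Mancl-DeRouen correction (divided by (2/3)²): SS/9 × 2.25 = SS/4. This needs |t| > 2.776 × √1.5 = 3.400, giving **2.7%**.

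**Mixed model.** Random hospital intercept fitted by REML, with the between-hospital variance truncated at zero. Simulated with 400,000 null data sets at ICC 0.015:

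| Comparison | Result |
|---|---|
| Mixed model, Wald z: null rejection | about 8.4% |
| Mixed model, t on 4 df: null rejection | 2.1% |
| Uncorrected GEE v Wald mixed model: different call at 0.05 | 10.0% |
| Uncorrected GEE v 4-df mixed model: different call | 16.4% |
| Kauermann-Carroll GEE (4 df) v 4-df mixed model: different call | 3.0% |
| Mancl-DeRouen GEE (4 df) v 4-df mixed model: different call | 2.3% |

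At ICC 0 and 0.05 the Wald mixed model rejects in about 4% and 11%; the uncorrected GEE stays at 18.5%.

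**Actual model fits.** Fitting both models to 600 simulated data sets gave 20.2% (uncorrected GEE), 9.7% (Wald mixed model) and 2.2% (4 df) with no effect. At a true effect of 0.3 SD the rates were 67.8%, 51.2% and 30.8%.

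**ER visits.** Assuming negative binomial counts with mean 0.8, dispersion 1 and between-hospital log-SD 0.1 (300 data sets), an uncorrected count GEE rejected in 22.3% and a linear mixed model in 7.0% with no effect. The two differed in 15.3%. Monte Carlo error in these smaller runs is about 1 to 3 points.

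**The case against.** **Section 14.B.4 may only summarize.** It has one general sentence on clustering, does not say that GEE replaces the mixed model, and is not an exclusive list, since it goes on to name Kaplan-Meier and Cox. One could read the Overview as the detail behind it, or the GEE sentence as meant for the primary outcome. That reading is possible. But the sentence directly follows the secondary comparison and carries no restriction, so the text needs clarifying.

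**The large error rates come mostly from having few clusters.** This stands. Once both methods use small-sample inference on 4 df, they disagree in only 2 to 3% of null data sets. A reader might infer that GEE is the wrong method, or that the trial's secondary false-positive rate is 18%. The documents do not support either: the protocol does not specify an uncorrected variance with a normal test, and such details are commonly left to a statistical analysis plan, which is not at hand.

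**A reader might also infer two conflicting p-values for every secondary endpoint.** That is too strong. The p-values usually differ but fall on opposite sides of 0.05 only in a minority of data sets. Survival is typed as continuous but has its own analysis. Service satisfaction is marked for the intervention group only in the section 11.A schedule, so under that schedule neither model gives a between-group test.

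**Retyping endpoints as counts is not enough.** This also stands. It would send them to a GEE without a stated correction and with a logit link, which suits a probability and not a Poisson or negative binomial mean.

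**Conclusion.** The point holds in limited form and should be fixed. For the between-group secondary endpoints other than survival and service satisfaction, the protocol supports two analyses that can give different p-values under its 0.05 rule. An unseen analysis plan cannot settle this without departing from one of the two passages.

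The size depends on small-sample handling: different significance calls in 10 to 16% of null data sets if GEE is uncorrected, and about 2 to 3% if both methods use 4 df. These figures assume ICC 0.015, six equal hospitals, normal outcomes and no baseline adjustment, although the Overview plans adjustment. The ER-visit figures rest on an assumed count distribution. The primary endpoint is assigned to a logistic GEE in both the Overview and section 6, so its model is not affected.

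**What to change.** - **Section 14.B.4:** limit GEE to dichotomous and count outcomes. Name the Overview's mixed model (random hospital intercept, small-sample degrees of freedom such as Kenward-Roger or Satterthwaite) as the single test for continuous outcomes other than survival.
- **Section 12.A.2:** type ER visits and the number of unscheduled hospitalizations as counts only.
- **Overview, Statistical Analysis:** replace the logit link for the Poisson or negative binomial model with a log link. State a small-sample-corrected variance with a t reference for the GEE analyses.

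The cost is a few sentences in three places and no change to data collection. The downside is wider intervals and lower nominal power for secondary endpoints. In the 0.3 SD example the 4-df mixed model rejects in 30.8% against 67.8% for uncorrected GEE, although the latter is inflated by its excess false positives. At ICC 0.015 the 4-df mixed model is also conservative (2.1% against a nominal 5%).

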|                              | 
2. Efficacy Endpoints
 
 
- Primary endpoint: The number of unscheduled hospitalizations within 6 months of study enrollment.
 
* Unscheduled hospitalization: This includes hospitalization at a respective participating institution for acute treatments (excluding scheduled hospitalizations for anti-cancer treatments, operations, and procedures), hospitalization at medical institutions other than the participating institutions, or hospitalization of 4 weeks or less at a nursing hospital.
 
- Secondary endpoint
 
 
n Patient: Medical service use (e.g., hospitalization and ER visit), critical care use (e.g., ICU admission and ventilator support), use of end-of-life medical services (e.g., ICU admission one month before death and ventilator support), satisfaction with the services, quality of life (ESAS and EQ5D), affective disorders (PHQ9), and preparation of advance directives.
 
n Guardian: Satisfaction with the services, quality of life (EQ5D), burden of care (CRA-K), affective disorders (PHQ9), and care competency.
 
n Costs: Medical expenses and care costs
                                                                                                                                                                                                                                                                                                                                                                                                                                                                                                                                                                                                                                                                                                                                                                                                                                                                                                                                                                                                     |

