## **C. Follow-up of Suspended Participants**

- Investigation of the medical records and secondary data linkage will be performed on the suspended participants from the time of suspension to the end of the remaining scheduled follow-up period (18 months after the registration) until no longer possible due to the participant's death, failure to follow-up, or withdrawal of consent. Any case of a patient receiving additional HBMC services (e.g., other HBMC pilot projects) other than the one provided in this clinical trial after the completion of the study will be recorded in the care

reports.

- For participants suspended due to reasons other than death, the follow-up survey will only be conducted with those who consent to participate via a telephone call made by a research nurse.

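### The logit link stated for the Poisson and negative binomial count models is wrong; it should be a log link (secondary count endpoints only)

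*Protocol*

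**What the plan says.** The Statistical Analysis row of the Protocol overview gives one rule for each type of outcome.

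- **Binary primary endpoint:** a GEE in which the intervention effect "will be evaluated using a logistic regression model based on the logit link function". The link is appropriate there.
- **Continuous outcomes:** a mixed model.
- **Counts:** "A GEE will be used to consider the patient clusters in the participating institutions", with a regression model that takes "Poisson and negative binomial as random components according to the distribution of variables using the logit link function as the link function".

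Section 12.A.2, Domain 1, lists two outcomes that are counts by nature: "Number of unscheduled hospitalizations within 6 months of study enrollment (continuous or count variable") and "Number of ER visits (continuous variable").

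On shortened follow-up, the same overview row says: "In the case of withdrawal of consent or dropout during follow-up, data collected till the time of withdrawal or dropout will be used". Section 13.C continues record review and data linkage for suspended participants to 18 months, "until no longer possible due to the participant's death, failure to follow-up, or withdrawal of consent".

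Section 14.B.4 repeats that GEE will be used and adds Kaplan-Meier and Cox methods for survival. It names no link for counts, so nothing in the protocol corrects the overview.

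**The concern.** Poisson and negative binomial models describe counts with no upper limit. The usual link is the log, which keeps the mean positive and makes the exponentiated coefficient a ratio of means. The logit is built for probabilities. Applied to a mean count it does two things:

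- It sets a ceiling of 1 on the fitted mean. Because the overview also plans to adjust for baseline differences, the ceiling applies to every combination of covariates and not only to the arm averages.
- It turns the treatment coefficient into a log ratio of mean/(1 − mean). That is neither a rate ratio nor, for a count, an odds ratio of anything.

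At stake is the estimate for the number of unscheduled hospitalizations, the first secondary endpoint in Section 12.A.2. A reader would naturally take the reported figure as a rate ratio, and it would look more favourable than the data. The phrase may have been carried over from the rule for the binary endpoint in the same row, where it is correct.

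**Working it through.** The protocol states no figure that rests on the count model, so there is none to reproduce. The link can be checked by algebra.

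**Inputs.** Family and link come from the overview. The true ratio of mean counts, R = 0.80, is an illustration in line with the 20% decrease hypothesised in Section 14.A. The control mean count μ₀ is an assumption, because the protocol gives none.

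**Step 1: range of the model.** With a logit link the mean is μ = 1/(1 + e^(−η)), which lies strictly between 0 and 1 for every η. No coefficient value gives a mean of 1 or more.

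**Step 2: what the coefficient estimates when both means are below 1.** With μ₁ = Rμ₀:

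exp(β) = [μ₁/(1 − μ₁)] / [μ₀/(1 − μ₀)] = R(1 − μ₀)/(1 − Rμ₀)

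For R below 1 the factor (1 − μ₀)/(1 − Rμ₀) is also below 1, so a reduction is always exaggerated. With a log link, exp(β) = μ₁/μ₀ = R at any mean.

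| Assumed μ₀ | μ₁ = 0.8μ₀ | Logit exp(β) | Reduction if read as a ratio of means | Log exp(β) |
|---|---|---|---|---|
| 0.1 | 0.08 | 0.72/0.92 = 0.783 | 22% | 0.80 |
| 0.3 | 0.24 | 0.56/0.76 = 0.737 | 26% | 0.80 |
| 0.5 | 0.40 | 0.40/0.60 = 0.667 | 33% | 0.80 |
| 0.8 | 0.64 | 0.16/0.36 = 0.444 | 56% | 0.80 |
| 0.95 | 0.76 | 0.04/0.24 = 0.167 | 83% | 0.80 |
| 1 or more | – | outside the model where a mean reaches 1 | – | 0.80 |

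**Step 3: numerical check.** Single simulated data sets (6 clusters of 66 patients) were fitted by GEE.

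- At assumed control means of 1.2 and 2.0, the logit fits returned no estimates for either family.
- At 0.5, the Poisson logit fit reproduced its observed means of 0.470 and 0.369 (ratio 0.785) but gave exp(β) = 0.659.
- At 0.5, the negative binomial logit fit ended at fitted means of zero. This is a numerical failure of that run: the algebra shows that observed means below 1 can be represented.
- All log-link fits converged.
- The software used (Python statsmodels) refuses the logit for the Poisson family unless its check is overridden.

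**Step 4: time at risk (secondary).** Without an offset, and if events occur at a constant rate, the expected ratio of counts is the true rate ratio multiplied by (mean follow-up in HBMC / mean follow-up in control). Take assumed follow-up fractions of 0.95 and 0.80 and a true rate ratio of 0.80:

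- HBMC followed longer: 0.80 × 0.95/0.80 = 0.95.
- HBMC followed for less time: 0.80 × 0.80/0.95 = 0.67.

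The direction depends wholly on which arm is followed for less time.

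**The case against.** Several stronger readings are tempting, and the protocol does not support them.

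**That the primary analysis is compromised.** The overview's list of endpoints does say "Primary endpoint: The number of unscheduled hospitalizations within 6 months of study enrollment". But the overview's sample size text, its Statistical Analysis row, Section 6 and Section 12.A.1 all treat the primary endpoint as binary and size or analyse it as a proportion. The stray line is a separate inconsistency. The logistic GEE and the sample size stand.

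**That the count model is bound to fail.** It breaks down only where a fitted mean reaches 1. The only event figures in the protocol, in the ICC table of Section 6, are 40/198 and 20/198, or about 20% and 10%. These are proportions with an event. They set a floor under the mean count and do not show it to be near 1. An analyst would also probably meet the error when programming, since software may reject the combination. Both points stand and limit the harm, but neither makes the written rule correct.

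**That ER visits are necessarily affected.** Section 12.A.2 labels them continuous, so the mixed-model rule may be the one intended. The logit error reaches them only if they are treated as a count, which by nature they are.

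**That the missing offset is an error in its own right.** An SAP could supply it, and the overview does not rule it out. Section 13.C keeps collecting records after suspension, so truncation is limited to death, loss to follow-up and withdrawal of consent. Nor can one say that the arm with more deaths will show fewer admissions: hospital use may rise near death, and the fourth hypothesis in the overview expects lower mortality under HBMC, which under a constant event rate would work against the intervention. Events per patient versus events per day alive is a choice of estimand. The offset is therefore a suggestion only.

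**Conclusion.** The point holds for the link function. The protocol states a count model with a link that does not suit counts, and no other section corrects it. The ceiling of 1 and the exaggeration of a reduction below 1 follow from algebra. The size of the exaggeration depends on mean counts that the protocol does not give. For a true ratio of 0.80 it is small at a control mean of 0.1 (0.783), material at 0.3 to 0.5 (0.737 to 0.667) and severe at 0.8 (0.444).

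The consequence is confined to secondary count endpoints: the number of unscheduled hospitalizations within 6 months and, if classed as a count, the number of ER visits. The ER label needs correcting in any case.

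**What to change.** In the count data paragraph of the overview's Statistical Analysis row:

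1. Replace the logit link by the log link for the Poisson and negative binomial models.
2. State that results will be reported as ratios of mean counts (rate ratios if an offset is used) with 95% confidence intervals.
3. In Section 12.A.2, class the numbers of unscheduled hospitalizations and of ER visits as counts, both analysed under this model.

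These are wording changes. They need no new data and leave the primary analysis and the sample size as they are.

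As a secondary suggestion, include an offset of log(days alive and under observation within 6 months), since data up to withdrawal or dropout will be used. It does not remove death as a competing event. Availability of dates should be checked first. The medical record table in Section 11.B covers death in hospital. Other deaths rely on linkage for consenting patients, and Section 11.C describes that linkage for the intervention group, whereas the overview does not restrict it to one arm.
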